### Study design and setting

The SoLID trial is a multi-centre prospective, randomised, single-blind (outcomes assessor), controlled, parallel assignment 3-year clinical trial (Figure 3). There will be accrual of participants over 24 months, and a follow up duration of 12 months. Participants will be randomly allocated to either low dialysate [Na+] of 135 mM or conventional dialysate [Na+] of 140 mM for 12 months duration, interventions that represent poles of customary practice with respect to dialysate [Na+] prescription in New Zealand. The trial will be conducted within 6 of the country’s 20 District Health Boards (DHBs), which are entities responsible for the provision of government-funded health and disability services in their geographical district. All of the DHBs in the SoLID trial provide renal services and have comprehensive home HD programmes: Counties Manukau, Waitemata, Auckland, Capital & Coast, and Canterbury. Participants will be either predominantly from urban settings (Counties Manukau, Waitemata and Auckland DHBs) or from a mixture of urban and rural ones (Capital & Coast, Canterbury, Waikato). For logistical reasons, no participant will be enrolled who lives more than 90–120 minutes from the hospital providing tertiary renal services.

**Figure 3 F3:**
[figure not shown]
The SoLID trial participant flowchart.

### Ethical considerations

Ethical approval has been obtained through the National (New Zealand) Multi-region Ethics Committee and each institutional review board within participating DHBs.

### Target population and eligibility criteria

The target population will be patients with ESKD on home HD. The particular sampling frame for the SoLID trial is chosen because home HD patients have the large attributable risk of death from CV as opposed to other causes [3], and a less “frail” phenotype compared to those dialysing in facilities with less tendency to intra-dialytic hypotension [123,124]. They are also the least likely dialysis patients to suffer from other inter-current illnesses that might result in their death or drop out from the trial (Figure 4), and are probably more likely to be compliant with the study procedures.

**Figure 4 F4:**
[figure not shown]
Kaplan-Meier estimates of non-death non-transplant censored home hemodialysis technique survival for the modern New Zealand population (2000–2010), from ANZDATA Registry; drop-out from home hemodialysis is 9.8% per year (15.3%, 53.6%, and 25.8% of drop-outs due to death, transplantation, and modality change respectively).

Eligibility criteria will include incident or prevalent patients treated with maintenance home HD under the care of the 6 participating DHBs who are; aged 18 years or older; suitable for both low and standard dialysate [Na+] in the view of their treating physician; have pre-dialysis plasma [Na+] ≥ 135 mM; and are willing to participate and able to provide consent.

Exclusion criteria will include HD treatments at a frequency greater than 3.5 times per week; treatment with maintenance hemodiafiltration; life expectancy of less than 12 months; scheduled for live donor kidney transplantation within 12 months of entry to the study; considered by the treating nephrologist to have concomitant illnesses or conditions that limit or contraindicate study procedures and follow-up (e.g. frequent intra-dialytic hypotension requiring fluid resuscitation); considered by the treating nephrologist to have a high chance of non-adherence to study treatments and non-attendance for procedures and follow up; current enrolment in clinical studies involving anti-hypertensive medications, changes in HD operating parameters, or any other intervention that is likely to confound the outcome of the trial; currently using sodium profiling during haemodialysis treatments; documented infiltrative cardiomyopathies (amyloid, glycogen storage disease), hereditary cardiomyopathies (hypertrophic cardiomyopathy) or moderate to severe aortic valve disease (aortic stenosis, regurgitation); inability to provide consent or follow study instructions due to mental health illnesses or conditions.

### Recruitment of participants

The research team at each site will utilise a purpose built pre-screening database in order to identify potential participants eligible for inclusion in the trial. Potential participants will then be approached by either their dialysis nurse, doctor or the trial research co-ordinator and formally invited to consider participation. After an initial explanation, we will provide further written information and schedule a follow-up meeting. At that meeting, potential participants will be able to meet the site investigator with a language interpreter as necessary, and ask any questions that arise from information that has provided. If the potential participant is willing to participate, they will provide written consent. Whenever a signed consent form is received from a patient they will be formally screened to confirm their eligibility and then enrolled in the trial. Patients who are approached but decline to participate or consent but are not eligible when screened will be recorded in a screening log and their care will continue in the usual fashion.

### Randomisation

Once baseline assessments have been completed and 28 days have elapsed since enrolment onto the trial, randomisation will be performed using a phone based interactive voice response system (IVRS) from the National (Australia) Health Medical Research Council (NHMRC), Clinical Trials Centre (CTC) Sydney, Australia. Participants will be randomised in computer generated blocks of random size (undisclosed), blinded to investigators, and stratified by a) treating centre, and b) whether they receive conventional (≤18 hours/week) or extended-hour (>18 hours/week) HD.

### Blinding

Baseline data will be collected prior to randomisation so that trial investigators, research co-ordinators and trial participants will be blinded to allocation while the baseline data is being collected. However, blinding will be not be maintained once randomisation has occurred. Assessors for the primary outcome of the study will be blinded for the duration of the trial. Assessors for the secondary outcomes of the study will not be blinded.

### Interventions

It has been previously estimated that high sodium exposure during HD for most populations would be characterized by dialysate [Na+] of ~141 mM, and low sodium exposure by dialysate [Na+] of ~135 mM [101]. Increasingly, there are calls by opinion leaders for individualised dialysate [Na+] prescriptions as being the most physiological approach to manage sodium balance. Individualised prescriptions can be achieved through the automated application of sodium kinetic (or conductivity) models, or the manual application of simplified algorithms based on patient pre-dialysis [Na+] [102,125-131]. However, preliminary research by the SoLID research team has suggested that natremic adaptation may in fact occur over time in response to altered dialysate [Na+] [89]. Moreover, there is no evidence that the results achieved using individualised dialysate [Na+] prescriptions are better than those achieved with the simpler and less expensive intervention of a fixed lower dialysate [Na+] applied to everyone. Consequently, dialysate [Na+] in our study arms will be fixed rather than individualised for all participants. A 2010 poll of dialysate [Na+] by the SoLID research team has shown that the median setting for the New Zealand centres was 139 mM.

Low Dialysate [Na+]: This group will undergo home HD with dialysate [Na+] of 135 mM for a duration of one year, introduced gradually by decrements of 1 mM/week over a 4–8 week run-in period as necessary. BP will be optimized by changes to target weight and antihypertensive medications according to a standardized protocol.

Standard Dialysate [Na+]: This group will undergo home HD with dialysate [Na+] of 140 mM for a duration of one year, similarly introduced by changes of 1 mM/week over an appropriate run-in period. BP will be optimised in an identical manner as above.

In the event of titration failure, the dialysate [Na+] level reached while aiming for the target level will be retained for the remainder of the follow-up, although such cases will be classified as being protocol violations.

Apart from dialysate [Na+], HD operating parameters for all participants will be managed in usual fashion according to local treatment goals. Dietary salt intake will be managed in all participants according local clinical practice guidelines [132], and monitored at baseline, 6months and 12 months using 3-day food diaries and analyses with Foodworks Pro® 9.0 (Xyris Software, Brisbane, Australia). Urinary Na+excretion will be monitored in all participants at baseline, 6 months and one year follow-up using inter-dialytic urine collection.

### Research outcomes and endpoints

The schedule of SoLID trial investigations and visits are summarised in Table 1, and outcomes are described below.

**Table 1 T1:** Schedule of participant investigations and visits

**Visit window (Days)**	**0 to28**	**28**	**28 to 42**	**42 up to 70**	**108 to 128**	**198 to 218**	**288 to 308**	**378 to 398**	^**+**^**7 up to **^**+**^**21**
**Visit name**	**BA/BR**		**T0**	**T1-T8**	**F3**	**F6**	**F9**	**F12/F12R**	**E1-E4**
**Study phase**	**Baseline assessment and results**	**Randomization**	**Titration (weekly)**		**Follow-up (3 monthly)**				**End (weekly)**
Randomization		X							
History	X					X		X	
Physical examination	X							X	
Non-interventional Titration			X						
Dialysate [Na^+^] Titration				X					
3day food diary	X					X		X	
Inter-dialytic urine for Na^+^ excretion	X					X		X	
Cardiac MRI	X							X	
ECF volume	X				X	X	X	X	
BP (intra-dialytic)	X			X	X	X	X	X	X
Ambulatory BP (inter-dialytic)	X							X	
Home BP (inter-dialytic)	X					X		X	
IDWG	X			X	X	X	X	X	
Antihypertensive medication history	X				X	X	X	X	
Dialysis Thirst Inventory	X					X		X	
Short Xerostomia Inventory	X					X		X	
Laboratory studies (NT-pro-BNP, hsCRP, urotensin II, plasma γNa / osmolality)	X				X	X	X	X	
Assessment of tolerance to HD	X			X	X	X	X	X	X
Arterial compliance (PWV)	X					X		X	
Arterial compliance (PWA)	X				X	X	X	X	
Quality of life (KDQOL)	X							X	
Quality of life (EQ-5D)	X							X	

#### Primary outcome – LV mass index

The primary outcome measure of the SoLID trial is LV mass index (LVMI), and the primary endpoint is LVMI at 12months. LVMI is also measured at baseline. LVMI will be measured using cardiac magnetic resonance imaging (MRI) imaging performed prior to HD treatments after a “long break” (the longest HD-free interval in any rolling schedule) or mid-week for participants who have fixed inter-dialytic intervals. All cardiac MRI scans will be performed at the local sites using a standardised protocol. Assessment of LV function will be performed using trueFISP cine imaging (6–7 short axis and 3 LV long axis with 20–30 cardiac phases depending on heart rate). Analysis of the images will be performed at a core laboratory at the Auckland MRI Research Group, University of Auckland, New Zealand. Each patient will have a four-dimensional mathematical model of the left ventricle created using guidepoint fitting. In all cases, volume, mass and wall thickness will be measured directly from the moving 3D curved surfaces which track the motion of the endo- and epicardium. This method has been validated for global parameters such as LV mass, end-diastolic volume, end-systolic volume, stroke volume and ejection fraction using global gold standard models [133]. All data will be analysed in duplicate by two independent and blinded analysts and the results reconciled in accordance with standard operating procedures of the group. Analysts will be monitored weekly for drift.

#### Secondary outcomes

##### LV volumes

LV volumes will be measured by cardiac MRI at baseline, and the endpoint will consist of follow-up measurements at 12 months. Measurements will be made used the same methodology used for LV mass index.

##### LV hemodynamics

LV hemodynamics will be as assessed by NT-pro-BNP (N-terminal pro brain natriuretic peptide) [134-140] and Urotensin II levels [141-145]. Measurements will be made at baseline, and the endpoints will consist of measurements at 3, 6, 9 and 12 months. All blood samples will be taken immediately prior to HD treatment following a “long break” or mid-week for participants who have fixed inter-dialytic intervals. All measurements will be made by the Christ church Cardiac Endocrine group in Christ church, New Zealand using the Elecsys® ProBNP assay (Roche Diagnostics Corporation, Indianapolis, IN, USA) and an in-house radioimmune assay for Urotensin II [146].

##### Extracellular fluid volume

ECF volume will be assessed by bioimpedance spectroscopy [147-149]. Measurements will be made at baseline, and the endpoints will consist of measurements at 3, 6, 9 and 12 months. All assessments will be performed immediately prior to HD treatments after a “long break” or mid-week for participants who have fixed inter-dialytic intervals. All measurements will be made using the Fresenius BCM monitor® (Fresenius Medical Care Australia Pty Ltd (New Zealand Branch), Auckland, New Zealand).

##### Blood pressure

BP will be assessed in the following ways;

a. Intra-dialytic BP (including pre- and post-dialysis BP). Measurements will be made at baseline, and the endpoints will consist of measurements at 3, 6, 9 and 12 months [150,151]. An additional endpoint will consist in the intra-dialytic blood pressure time-averaged over the individual follow-up period, using all available measurements accepting that there may be differing numbers of measurements per participant and time point.

b. Inter-dialytic BP assessed by the gold standard of ambulatory monitoring [150,152-155]. Measurement will be made at baseline, and the endpoint will consist of measurement at 12 months. All assessments will be performed according to the ‘Practice Guidelines of the European Society of Hypertension’ for clinic, ambulatory and self BP measurement [156]. Systolic and diastolic BP measurements will be made at 30 minute measurement intervals for 44 hours during a “long break” or mid-week for participants who have fixed inter-dialytic intervals. All measurements will be made using Oscar 2 ambulatory BP monitors (Suntech Medical Instruments, Raleigh, NC, USA). Measurements will be made on the non-access arm, and the measurement arm will be kept consistent during the study. Ambulatory BP monitoring will be considered adequate if at least two-thirds of the measurements taken over the 44-hour period are satisfactory [156].

c. Inter-dialytic BP determined as the weekly average of home blood pressure readings, an independently validated approach [150,157,158]. Measurements will be made at baseline, and the endpoints will consist of measurements at 6 and 12 months. Measurements will made using the Omron HEM-791IT Blood Pressure Monitor (Omron Healthcare Inc, Lake Forest, IL, USA). Readings will be made 3 times per day (on waking up, between noon and 1900, and before bed) during the 7days immediately prior to 3, 6, 9 and 12 months [150,157,158].

d. The number and dose of anti-hypertensive medications (expressed as the aggregated% of maximum recommended daily dose) [159]. Measurements will be made at baseline, and the endpoints will consist of measurements at 3, 6, 9 and 12 months.

##### Inter-dialytic weight gain (IDWG)

IDWG will be calculated by the difference between pre- and- post dialysis weight. Measurements will be made at baseline, and the endpoints will consist of measurements at 3, 6, 9 and 12 months. An additional endpoint will consist in the inter-dialytic weight gain time-averaged over the individual follow-up.

##### Thirst and xerostomia

Thirst and xerostomia will be assessed by visual analogue scale using standardised validated inventories [160-163]. Measurements will be made at baseline, and the endpoints will consist of measurements at 3, 6, 9 and 12 months.

##### High sensitivity C-reactive protein (hsCRP)

Long term CV mortality risk will be assessed by hsCRP [164]. Measurements will be made at baseline, and the endpoints will consist of measurements at 3, 6, 9 and 12 months. All blood samples will be taken immediately prior to HD treatment following a “long break” or mid-week for participants who have fixed inter-dialytic intervals. All measurements will be made using the Abbott Architect® Analyser and CRP Vario® latex immunoassay (Abbott Park, IL, U.S.A).

##### Arterial compliance

Arterial stiffness will be assessed by carotid-femoral Pulse Wave Velocity (PWV) and by radial Pulse Wave Analysis (PWA, deriving both central pulse pressure and the augmentation of the central pulse waveform at the radial artery). The methodology represents the current gold standard for non-invasive measurement of aortic arterial stiffness [165]. Pulse Wave Velocity measurements will be made at baseline, and the endpoints will consist of measurements at 3, 6, 9 and 12 months. Pulse Wave Analysis measurements will be made at baseline, and the endpoints will consist of measurements at 6 and 12 months. Assessments will be performed immediately prior to HD treatments after a “long break” or mid-week for participants who have fixed inter-dialytic intervals. Measurements will be made using the SphygmoCor® device (AtCor Medical, West Ryde, Australia) which employs applanation tonometry to measure the shape and velocity of the pulse wave, with good repeatability and reproducibility. Both PWV and PWA measurements will be measured in duplicate. If the difference between the two PWV measurements is > 10%, a third measurement will be performed and the average the two most similar measurements used. For quality control, the Sphygmocor calculates the standard deviation (SD) of the pulse transit time (PTT) over the 10 second waveform capture period. A carotid-femoral PTT SD of < 20% in dialysis patients is considered by the manufacturers to indicate a good quality measurement for PWV and will be the accepted maximum carotid-femoral PTT SD for measurements in this trial.

##### Pre-dialysis plasma sodium ionic activity (γNa)

Pre-dialysis plasma γNa and osmolality will be assessed at baseline, and the endpoints will consist of measurements at 3, 6, 9 and 12 months. All blood samples will be taken immediately prior to HD treatment following a “long break” or mid-week for participants who have fixed inter-dialytic intervals. Plasma γNa measurements will be made by direct inometry using an ABL800 or ABL83 blood gas analyser (Radiometer, Copenhagen, Denmark) and corrected by a factor of 0.967 to account for the Donan Effect from negatively charged plasma proteins [166]. Plasma osmolality will be analysed by freezing point depression using the Advanced® Model 3320 Micro-Osmometer (Advanced Instruments, Norwood, MA, USA).

##### Health related quality of life

Consistent with previous recommendations [167-169], health related quality of life (HRQoL) will be assessed using a spectrum of validated instruments. Measurement will be made at baseline, and the endpoint will consist of measurement at 12 months. Measurements will be made using the Kidney Disease Quality of Life (KDQOL) [170-172] and the preference based EuroQol EQ-5D questionnaires [167,173].

#### Tolerability outcome

##### Tolerance to dialysis

Tolerance to dialysis will be assessed by the frequency of intra-dialytic hypotension episodes in the two weeks prior to the assessment time point. Hypotension episodes will be identified according to the NKF-K/DOQI definition (a decrease in systolic BP by ≥20 mMHg or a decrease in mean arterial pressure by ≥10 mMHg associated with one or more of the following symptoms: abdominal discomfort, nausea, vomiting, muscle cramps, restlessness, dizziness, fainting, anxiety and the requirement for fluid boluses) [164]. Measurements will be made at baseline, and the endpoints will consist of measurements at 3, 6, 9 and 12 months. An additional tolerance endpoint will consist in the time-averaged frequency of hypotension episodes over the individual follow-up period.

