However, the potential benefits of lower dialysate [Na+] should be weighed against a potential “dark side”. Several large and well performed observational analyses have shown an association between lower dialysate [Na+] and higher mortality risk, notably in those patients with a “frail” phenotype characterized by low serum [Na+], diabetes mellitus, coronary artery disease, CV disease, congestive heart failure, cerebrovascular disease, lung disease, and cancer [72,92,93]. The most plausible explanation for these observations relates to decreased hemodynamic stability with lower dialysate [Na+], and the vulnerability of “frail” patients to intra-dialytic hypotension, an unquestionably threatening condition associated with myocardial stunning and all-cause patient mortality [94-99]. Intra-dialytic hypotension is ameliorated by higher dialysate [Na+], and is likely to be at least as deleterious (if not more so) as inter-dialytic hypertension.

Another concern with lower dialysate [Na+] is that it might influence serum [Na+]. Humans are considered to have an individual natremic set point, and most observational studies have not shown any cross-sectional correlation between dialysate and serum [Na+] [67,73,100-105]. However, pre-dialysis serum [Na+] did change in several small prospective clinical trials after changes to dialysate [Na+] [54,58,62,64,89,106,107], albeit often after a lag of several months possibly due to the large reservoirs of non-osmotic sodium in skin and bone [108-111]. There is a clear association between low serum [Na+] and patient mortality in patients with kidney disease, and an intervention that might potentially lower serum [Na+] warrants careful scrutiny [112-114].

A final concern is raised by clinical trials of dietary salt reduction in non-ESKD populations. Overall, there is higher mortality and morbidity in those participants who had the lowest salt intake, especially in the setting of generally low salt consumption [115-117]. A number of plausible biological mechanisms might be contributing to the poorer outcomes among those with low salt intake, involving several key metabolic and neurohormonal pathways (e.g. activation of sympathetic nervous and renin–angiotensin systems, increased in total and low-density lipoprotein cholesterol, reduction in peripheral insulin sensitivity etc.) [118-121].

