In terms of internal validity, the strengths of the SoLID trial are that it is prospective and randomised, with robust allocation concealment and analysis of cardiac MRI data in duplicate by two blinded independent analysts who will remain unaware of the allocation of participants for the duration of the trial. A limitation of the trial pertains to secondary outcomes. All baseline measurements of secondary outcomes will be made prior to randomisation. However, once randomisation has occurred, participants and assessors for the follow-up measurements will not be blinded to treatment. For instance, bioimpedance and pulse wave procedures and measurements will be performed by research associates who will be potentially aware of the allocation of participants. This may bias participants’ and research associates’ perception of tolerance to the intervention, and their reporting of subjective scoring surveys such as thirst and xerostomia inventories and HRQoL questionnaires. The impact of any actual bias is likely to be mitigated through completion is baseline measurements prior to randomisation, but certainly not abrogated.

Of note, the SoLID Trial excludes those who are on dialysis more than 3.5 times per week to avoid confounding the effect of dialysate [Na+] on LV mass by frequent or nocturnal dialysis. The study will not exclude those whose HD treatments are unconventionally long (~8 hours per treatment) so long as they are undergoing HD no more than 3.5 times per week. This is based on the high reported prevalence of LV hypertrophy in populations treated with this manner (notwithstanding the overestimation of LV mass by echocardiography that biases these studies [175]): 87% of patients in Christchurch NZ [124], 76% of those in Manchester UK [177], and in more than 80% of those in Tassin France [178]. LV hypertrophy is still present in these populations on long-hour dialysis as a result of BP variability, neurohormonal factors and residual positive sodium balance, all of which are potentially modifiable with lower dialysate [Na+].

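### The hypotension count ties a blood-pressure fall to mostly subjective symptoms under open allocation, and no count on the blood-pressure criterion alone is described beside it

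*Protocol article*

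**What the plan says.** **Endpoint.** Under Tolerance to dialysis, the protocol article states: "Tolerance to dialysis will be assessed by the frequency of intra-dialytic hypotension episodes in the two weeks prior to the assessment time point". The pressure part of the definition, attributed to NKF-K/DOQI, is "a decrease in systolic BP by ≥20 mMHg or a decrease in mean arterial pressure by ≥10 mMHg". The symptom condition is attached to it in the words "a decrease in mean arterial pressure by ≥10 mMHg associated with one or more of the following symptoms". A list of associated items follows, opening with abdominal discomfort, nausea and vomiting and ending with "muscle cramps, restlessness, dizziness, fainting, anxiety and the requirement for fluid boluses".

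**Analysis.** The Tolerability analysis section applies negative binomial regression to this count, with a mixed-effects version for trends over time. The tolerability row of Table 2 names hypotension event counts and nothing else.

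**Blinding and setting.** The target population dialyses at home. The Blinding section says: "Assessors for the secondary outcomes of the study will not be blinded". The Discussion adds that "once randomisation has occurred, participants and assessors for the follow-up measurements will not be blinded to treatment". It accepts that this may bias perceived tolerance, and says that pre-randomisation baseline measurement reduces the bias without removing it.

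**Importance of the harm.** The Background gives reduced haemodynamic stability as the most plausible explanation for the excess mortality seen with low dialysate sodium in observational data. It calls intra-dialytic hypotension "an unquestionably threatening condition associated with myocardial stunning and all-cause patient mortality". The secondary hypothesis is that tolerance is non-inferior.

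**Related endpoint.** Under Blood pressure, "Intra-dialytic BP (including pre- and post-dialysis BP") is measured at baseline and at 3, 6, 9 and 12 months, and is also averaged over follow-up.

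**The concern.** A pressure fall enters the count only if something else accompanies it, and that something is usually a sensation that a person notices and mentions. Nausea, restlessness, dizziness and anxiety are plainly of this kind. When allocation is known, the readiness to notice and mention them can differ between arms. The count is then the product of two quantities, how often pressure falls and how often a fall is accompanied by a listed item, and the analysis cannot separate them.

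The comparison at stake is the harm that the Background treats as the main reason for caution. Under-reporting in the low-sodium arm would favour the trial's own hypothesis of non-inferior tolerance. Over-reporting would suggest a harm that pressure readings might not support. In either case a fall without a listed item is not an episode, and no other described endpoint counts it.

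**Working it through.** **1. Is there a stated figure to reproduce?** No. The article gives no expected episode rate, no reporting rate and no power for this endpoint. The check is therefore a reading of the text followed by an illustration on assumed inputs.

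**2. What the wording counts.** The sentence can be read in two ways, according to whether the symptom condition attaches to both pressure criteria or only to the one before it.

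| Event | Condition on both criteria (natural reading) | Condition on mean arterial criterion only |
|---|---|---|
| Systolic fall of at least 20 mmHg, listed item present | counted | counted |
| Systolic fall of at least 20 mmHg, no listed item | not counted | counted |
| Mean arterial fall of at least 10 mmHg only, listed item present | counted | counted |
| Mean arterial fall of at least 10 mmHg only, no listed item | not counted | not counted |

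The choice of reading changes the count in the second row.

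**3. Does another endpoint count the falls?** Intra-dialytic pressure carries no symptom condition, and Table 1 schedules it at the same visits as the tolerance assessment. It is analysed as a level, by visit and time-averaged. The secondary hypothesis treats better pressure control as a benefit, so a lower average would read as efficacy. An average does not show how often pressure dropped within sessions.

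**4. How reporting enters the comparison.** Let RR be the true ratio of pressure-qualifying falls (low sodium to standard), and let s be the share of falls in each arm that meet the symptom condition. Then

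apparent rate ratio = RR × (s_low / s_std).

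The documents give no value for s, so every share below is an assumption.

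| True RR | s_std | s_low | Calculation | Apparent ratio |
|---|---|---|---|---|
| 1.0 | 60% | 75% | 0.75 / 0.60 | 1.25 |
| 1.0 | 60% | 45% | 0.45 / 0.60 | 0.75 |
| 1.0 | 50% | 60% | 0.60 / 0.50 | 1.20 |
| 1.0 | 50% | 40% | 0.40 / 0.50 | 0.80 |
| 1.0 | 50% | 75% | 0.75 / 0.50 | 1.50 |
| 1.0 | 50% | one third | 0.333 / 0.50 | 0.67 |
| 1.5 | 50% | one third | 1.5 × 0.333 / 0.50 | 1.00 |
| 1.5 | 50% | 75% | 1.5 × 0.75 / 0.50 | 2.25 |

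Equal shares leave the ratio unbiased, however low they are. Only a difference between arms distorts it, and that difference can create a signal where none exists or hide a true ratio of 1.5.

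**The case against.** The strongest case for leaving the plan alone has four parts.

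- **The definition is a named, published one, and the outcome is called tolerance.** Requiring a clinical consequence is coherent for that purpose. A different symptom share could even be a real effect of the intervention and not a reporting artefact. This stands, and is why the endpoint should be kept.
- **The list is not purely subjective.** Vomiting and fainting are observable, and a need for fluid boluses is a treatment need. A reader might infer that a fall counts only if someone complains of a symptom. The text does not support that, although at home the bolus item may itself reflect an unblinded decision.
- **Pressure is analysed separately.** A reader might infer that silent falls leave no trace in the trial. That is too strong: they are missing from the episode count on the natural reading, but the readings feed a pressure endpoint. What stands of the concern is that this endpoint does not count falls.
- **The limitation is disclosed, and a supplementary count is something a condensed article may leave elsewhere.** The disclosure is fair, and the point is neither a contradiction nor an error. But disclosure does not correct the bias, and the point concerns a definition that the article does state.

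Two further limits apply. The article does not say who records symptoms, so self-reporting by participants is a reasonable inference and not a documented fact. It also does not say that every session in each two-week window has systematic readings. If extra readings are taken when someone feels unwell, a count based on pressure alone inherits the same bias.

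**Conclusion.** The concern holds as a design weakness worth correcting. The tolerability comparison rests on a count in which most qualifying items are subjective and in which participants and follow-up assessors know the allocation. No described endpoint shows how often pressure fell regardless of symptoms. The wording also leaves open which pressure criterion the symptom condition governs.

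The size and direction of any bias cannot be obtained from the documents. Under the assumed shares, equal true rates can appear as ratios from 0.67 to 1.50. These figures show the mechanism and are not estimates for this trial. A reader might infer that the trial cannot distinguish a haemodynamic effect from reporting at all, or that bias has been demonstrated. Neither follows: the separate pressure endpoint gives some haemodynamic information, and differential reporting is a possibility, not a finding.

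**What to change.** Keep the present endpoint and make these changes:

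1. State whether the symptom condition applies to both pressure criteria or only to the mean arterial one.
2. Pre-specify a supportive count of sessions, in the same two-week windows, whose recorded readings meet the pressure part of the definition regardless of symptoms. Analyse it with the same negative binomial model.
3. Report by arm the number of sessions and of readings available in those windows, so that uneven measurement can be seen.
4. Report both treatment estimates with 95% confidence intervals, and interpret a divergence as possible reporting bias. Because one count is of episodes and the other of sessions, compare the rate ratios and not the raw counts.
5. Include both counts in the six-monthly safety reports to the Data Monitoring Committee.

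It may be tempting to allow a tolerability conclusion only if both counts point the same way. That rule should not be used: it has no stated error properties, and with near-equal arms two noisy counts can differ in sign by chance, so the less specific count would act as a veto.

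The cost is one further analysis, using readings that the present definition already needs. The drawback is lower specificity, since minor falls will be included, and the count is only as unbiased as the session readings are systematic. It therefore supports the present endpoint and does not replace it.
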